#### Overview of intervention period

Participants in both conditions will receive a welcome message 2 days after the baseline survey is completed to confirm enrolment and maintain contact while onboarding procedures are completed. Participants allocated to the RISE intervention will also be contacted by telephone to confirm their preferred messaging times and where applicable to organise the delivery of the wearable device (Garmin or Empatica EmbracePlus; device type dependent on availability) prior to commencement of the intervention. Instructions for setting up and using the device will also be provided. Participants will be instructed to wear the wearable device as much as possible over the entire intervention period, except when charging, as we are interested in both activity and sleep data. Participants in the RISE group will also be advised of the interactive nature of the intervention, including two-way messaging features, and offered optional support phone (audio-only) sessions during the intervention period, including one 30-min telephone session with a psychologist (or provisional psychologist) and one 30-min telephone session with a physiotherapist trained in the delivery of simple stress management techniques. Sessions will be scheduled as required. These onboarding procedures ensure participants are prepared to receive the RISE intervention and wearable devices prior to message delivery.

Seven days after the baseline survey is completed, participants will begin to receive the onboarding text messages relevant to their assigned condition. This timeframe allows for participants to receive the smartwatch. The onboarding message series will be delivered over 2 days to minimise burden and information overload. These messages will inform participants that they can pause or withdraw from the study at any point by texting SNOOZE or STOP to the trial’s dedicated mobile number. The messages will also include information on the research team, on-demand messages, two-way messaging options and emergency contact details. Prior to commencement of daily messages, a message will be sent to confirm that the wearable device has been set up and is working.

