### Process evaluation

A process evaluation will focus on key implementation outcomes,^25^ including acceptability, feasibility and perceived appropriateness of the RISE intervention. Following completion of the post-assessment questionnaire, a purposive sample of approximately 10 participants from the RISE intervention group will be invited to complete a semi-structured interview exploring their experience of the RISE intervention including barriers and enablers to participation and suggestions for improvement. Sampling will aim to capture variation in recruitment site, level of intervention engagement and participant experience to obtain a diverse range of perspectives on acceptability and implementation. Participants will receive $50 for completing a 60-min interview. In addition, patients, health professionals and funders (compulsory third-party (CTP) insurance representatives) (total approximately n=10) will be purposively sampled and invited to participate in a series of 2–3 focus groups (or individual interviews if required) to explore opportunities to optimise and integrate RISE into healthcare settings and insurance system care pathways. Patient participants will receive $50/hour for participating in focus groups. These sample sizes are pragmatic and appropriate for a feasibility study and are intended to capture a range of experiences and perspectives to inform intervention refinement and implementation planning rather than to achieve thematic saturation. Findings from the process evaluation will be used to contextualise feasibility outcomes, including recruitment, retention and intervention engagement and to inform interpretation of preliminary clinical outcomes.

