#### Personalisation of the RISE intervention

The RISE intervention incorporates a range of personalisation features within both message content and delivery to support relevance and responsiveness to individual participant needs and preferences over the intervention period. During onboarding, participants nominate their preferred time of message delivery and are offered the option to schedule one 30-min session with a psychologist and one 30-min session with a physiotherapist trained in StressModex (integrated stress inoculation training and exercise)^13^ at any point during the programme. Throughout the intervention, participants can access additional messages on demand via keyword text requests (eg, CALM, ACTIVATE). At the end of week 1, participants receive a prompt to review message frequency and may choose to reduce frequency for a 24-hour period. In addition, participants can temporarily reduce message frequency at any time by texting SNOOZE. Message content is further tailored during weeks 1–3 based on baseline survey responses (eg, sleep disturbance, concentration difficulties), and participants receive two-way SMS check-ins during this period to rate pain intensity, stress and perceived support. Participants are also invited to complete a brief weekly check-in survey and diary entry to reflect on their experiences. At the end of week 3, participants are offered the option to extend messaging for an additional 3 days. These features provide a structured approach to tailoring intervention delivery while maintaining consistency across participants.

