#### Acceptability

An adapted version of the Technology Acceptance Model (TAM)^29^ will be used to assess perceived ease of use and perceived usefulness of the RISE intervention. Each construct is measured using six items rated on a 7-point scale from 1 (‘Strongly disagree’) to 7 (‘Strongly agree’). Mean scores will be calculated for each subscale, and participants will be classified as meeting the acceptability criterion if both subscale mean scores are≥4.0. TAM items will be framed in the future tense at baseline to assess anticipated acceptability and in the past tense at follow-up to assess experienced acceptability following intervention use.^30^

Additional indicators of acceptability will include responses to purpose-built items, including participant intention to use (or continue using) the intervention, willingness to recommend the intervention to others with WAD and Session Rating Scale scores for participants who complete the clinician-guided session/s.^31^ Intervention-specific items assessing perceived informational support, emotional support, encouragement for behaviour change and confidence in managing recovery will also be included. These items were developed to align with the core domains of the RISE intervention. In addition, behavioural indicators of acceptability will be examined and summarised. These include participant engagement with optional or self-initiated features, such as use of the on-demand message function, ‘snooze’ or ‘stop’ functions and weekly diaries, as well as the frequency of use of these features. Participant feedback on message frequency and perceived helpfulness will also be assessed. These behavioural indicators provide additional insight into patterns of participant engagement beyond the core intervention components. Finally, we will examine time participants wear the device, including the extent of valid data derived from the wearable device.

Patient experience and clinician and funder perspectives, including those of CTP insurance representatives, will be explored as part of the process evaluation. Individual semi-structured interviews and focus groups will examine the perceived value and implementation potential of the RISE intervention as well as opportunities for optimisation. Sessions will be co-facilitated by research staff experienced in co-design and qualitative methods, audio-recorded and transcribed verbatim.

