### Data analysis

Participant characteristics and baseline measures will be summarised using descriptive statistics. As this is a feasibility trial, analyses will be primarily descriptive and will focus on estimating feasibility parameters. Feasibility outcomes (recruitment, retention, intervention engagement, data completeness and acceptability) will be descriptively summarised. These estimates will be interpreted against the pre-defined progression criteria (see table 2) together with the process evaluation data to determine whether a future definitive trial is warranted. Final progression decisions will be made by the Trial Management Committee based on the overall pattern of feasibility findings across domains, together with qualitative process data and consideration of whether any identified barriers are modifiable. Where findings are mixed, decisions regarding progression will consider the pattern of results across domains, the nature and modifiability of barriers and the potential for refinements prior to a future trial. Participant responses regarding treatment allocation will also be summarised descriptively and compared with actual allocation to assess the success of participant blinding. No formal imputation of missing data is planned. The extent and patterns of missing data will be examined as part of the feasibility evaluation of the data collection procedures.

Preliminary changes in patient-reported outcomes will be explored using estimates of between-group differences with 95% CIs at each follow-up time point. These analyses will be conducted on an intention-to-treat basis. As this feasibility study is not powered to evaluate clinical effectiveness, no formal hypothesis testing will be undertaken and estimates will be interpreted cautiously with consideration of the width of the CIs. These exploratory analyses are intended to identify preliminary signals of potential clinical benefit, assess the suitability and responsiveness of candidate outcomes and inform the selection of the primary clinical outcome for a future definitive trial.

Qualitative interview and focus group data will be analysed using reflexive thematic analysis^44

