### Ethics and dissemination

Ethical approval for this study has been obtained from the Townsville Hospital and Health Service Human Research Ethics Committee (HREC/QTHS/121395) and ratified by The University of Queensland Human Research Ethics Committee (2025/HE002491). The study will be conducted in accordance with the National Health and Medical Research Council National Statement on Ethical Conduct in Human Research (2007, updated 2018) and the principles of the Declaration of Helsinki.

All participants will provide informed consent prior to participation (see online supplemental material for a copy of the participate information and consent form). For participants recruited via hospital services, a member of the treating team or research staff will introduce the study with verbal consent obtained prior to sharing participant contact details for the research team to follow-up. Participants can also contact the research team directly if they receive a letter or see study advertisements. Participation is voluntary and participants may withdraw at any time without consequence to their care.

Given the nature of the co-designed intervention, risks to participants are considered low. The RISE intervention consists of supportive and informational text messages designed to promote recovery. Participants will be able to opt out of receiving messages at any time (eg, by replying ‘STOP’) or temporarily pause messages if desired. While the content is not intended to replace clinical care, participants will be encouraged to seek appropriate medical advice if symptoms worsen or concerns arise. Any adverse events or participant concerns raised during the trial will be monitored and managed in accordance with study protocols.

Participant confidentiality will be maintained throughout the study. Data will be de-identified and stored securely on password-protected servers at The University of Queensland. Only authorised members of the research team will have access to identifiable data. Any data used for analysis and dissemination will be reported in aggregate form to ensure participants cannot be identified.

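### STOP (and SNOOZE) are defined inconsistently, as leaving the study in one section and as a message setting in others, so stopping messages could also end data collection

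*Protocol article*

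**What the plan says.** All places are in the protocol article.

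- **STOP as study withdrawal.** Under Overview of intervention period, the onboarding messages inform participants that "they can pause or withdraw from the study at any point by texting SNOOZE or STOP". The sentence covers the onboarding messages for either condition.
- **STOP as message opt-out.** Under Ethics and dissemination, participants can "opt out of receiving messages at any time (eg, by replying ‘STOP’) or temporarily pause messages if desired". The same section deals with leaving the study in a different sentence, which names no keyword: "Participation is voluntary and participants may withdraw at any time without consequence to their care".
- **STOP as an outcome.** Under Acceptability, the behavioural indicators cover engagement with optional features, "such as use of the on-demand message function, ‘snooze’ or ‘stop’ functions and weekly diaries".
- **SNOOZE.** It pauses the study in the onboarding sentence. Under Personalisation of the RISE intervention, "participants can temporarily reduce message frequency at any time by texting SNOOZE". The ethics section speaks of a temporary pause in messages.
- **Follow-up and analysis.** Post-intervention assessments asks every participant for the 6-week and 3-month questionnaires, by an emailed or texted link. Feasibility outcomes and key feasibility criteria takes retention over all randomised participants and acceptability over those allocated to RISE. Data analysis says of the between-group estimates: "These analyses will be conducted on an intention-to-treat basis". It plans no formal imputation.
- **Interviews.** Under Process evaluation: "Following completion of the post-assessment questionnaire, a purposive sample of approximately 10 participants from the RISE intervention group will be invited". Sampling is meant to vary by site, engagement and experience.

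**The concern.** One keyword cannot be both a record of how someone used the intervention and a notice that they have left the trial. Someone who has been told that STOP withdraws them, and who then texts it, has on the plain meaning ended participation. Sending that person the later questionnaires becomes questionable, yet the follow-up plan assumes that they will be sent.

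Three things are exposed if STOP is handled as withdrawal:

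- Retention would mix dislike of the messages with loss to follow-up.
- Acceptability could be reported mainly by people who kept the messages.
- The intention-to-treat estimates, with nothing imputed, would lose some people because of how they responded to the intervention.

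The first two matter most, because the progression criteria are the trial's primary purpose.

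**Working it through.** No figure in the plan needs reproducing here. The check compares the texts and then illustrates the size. The numbers of STOP users, the other non-response, the count meeting the acceptability criterion and the outcome gaps are all assumptions; the article gives none of them.

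**1. Texts side by side**

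| Section | STOP | SNOOZE |
|---|---|---|
| Overview of intervention period | leaves the study | pauses the study |
| Ethics and dissemination | ends messages; withdrawal stated apart | pauses messages (keyword not named) |
| Acceptability | a feature whose use is counted | a feature whose use is counted |
| Personalisation of the RISE intervention | not mentioned | lowers message frequency for a time |

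The Acceptability entry fits a message-level meaning. Only the onboarding sentence makes either keyword act on study participation.

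**2. Retention**

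Inputs: 50 randomised; green 70%, amber 50–69% (Table 2).

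- Each STOP user who would otherwise have responded costs 1/50 = 2 percentage points.
- Assume 25% non-response for other reasons, and s STOP users treated as withdrawn. Retention = 0.75 × (50 − s)/50.
- s = 0: 75% (green). s = 2: 0.75 × 48/50 = 72% (green). s = 4: 0.75 × 46/50 = 69% (amber). s = 8: 0.75 × 42/50 = 63% (amber).

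The effect is downward, because those lost stay in the denominator.

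**3. Acceptability**

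Inputs: 25 allocated to RISE; green 60%, amber 40–59% (Table 2). Assume 14 meet the criterion and STOP users do not.

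- All allocated: 14/25 = 56% (amber), however many STOP users there are.
- Completers only, 1 lost: 14/24 = 58.3%. 2 lost: 14/23 = 60.9% (green). 5 lost: 14/20 = 70% (green).

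The inflation appears only with a completers-only denominator.

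**4. Between-group estimates**

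Assume a share f is lost from RISE only, with outcomes d SD worse than those who remain. The complete-case mean then shifts by f × d.

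- f = 2/25 = 8%, d from 0.25 to 1.0: 0.02 to 0.08 SD.
- f = 5/25 = 20%, d from 0.25 to 1.0: 0.05 to 0.20 SD.
- Approximate 95% CI half-width, unadjusted, in SD units: 1.96 × √(1/25 + 1/25) = 0.55 with 25 v 25; 1.96 × √(1/20 + 1/25) = 0.59 with 20 v 25.

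In these scenarios the shift is well inside the half-width.

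**The case against.** A reader might infer that the plan removes people who dislike the messages from follow-up and so biases retention, acceptability and the clinical estimates. The documents do not support that:

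- **No exclusion is stated.** Both questionnaires go to all participants, retention is over all randomised, and the estimates are by intention to treat. The onboarding sentence is a short paraphrase of a text message and may be loose drafting. The SMS itself and the consent form are not shown and may already separate the two events.
- **Retention would not be flattered.** It would fall, which makes the criterion harder to meet.
- **Inflated acceptability needs a denominator that the article does not state.** The stated population is those allocated to RISE, which more naturally gives 25.
- **More STOP use in RISE is conjecture.** RISE sends more messages, but its participants can choose delivery times, review frequency and snooze, and are paid extra for wearable use and check-ins. Controls have no personalisation.
- **Stoppers would not go wholly unheard.** Keyword use is recorded without a questionnaire, interview sampling seeks varied engagement, and the reference to the post-assessment questionnaire may describe timing rather than a condition.
- **The clinical estimates carry little weight.** There is no hypothesis testing, cautious interpretation is promised, and missing-data patterns will be examined.

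All of this stands as a limit on the consequences. It does not remove the contradiction, which concerns an instruction given to participants. The provisions for full follow-up also show that the onboarding wording works against the trial's own plan.

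**Conclusion.** The contradiction is real and should be corrected before the first participant is onboarded, since follow-up lost to the wording may not be recoverable. It is a fault of wording and data capture that could cause loss of data, not a demonstrated bias.

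If STOP were handled as withdrawal, the likely effects are:

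- **Retention:** lower, by 2 points for each STOP user who would otherwise have responded. With 25% other non-response, four such users move it from green to amber.
- **Acceptability:** possibly inflated, and only if people without data leave the denominator. In the example two losses are enough to turn amber to green.
- **Between-group differences:** possibly a selective loss, of 0.02 to 0.20 SD in the scenarios tried, against a CI half-width of about 0.55 to 0.59 SD.

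The direction and size in this trial depend on how many people text STOP, in which arm, and how staff then treat them. None of these is known.

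**What to change.** - Align Overview of intervention period, Personalisation of the RISE intervention, Acceptability, and Ethics and dissemination so that STOP and SNOOZE act on messages only, with one description of each, and study withdrawal is a separate request.
- State that STOP users are still sent the 6-week and 3-month questionnaires unless they separately decline data collection.
- Record message opt-out and study withdrawal as separate fields, each dated.
- Calculate the acceptability percentage over all participants allocated to RISE, and report how many have no acceptability data.
- Allow the existing interviews (about 10) to include people who texted STOP.

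The cost is one reworded onboarding SMS, a check that the consent text agrees with it, and one additional REDCap field. No extra interviews are needed. The acceptability figure may look less favourable.

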#### Post-intervention assessments

All participants will be asked to complete an online assessment questionnaire at 6-week post-randomisation and at a 3-month follow-up. The questionnaire is completed online, and participants will be sent a link via email (or SMS) where they can access it. All participants will be remunerated $30 for each questionnaire completed (based on Health Consumer Queensland guidelines).

A summary of the proposed data collection schedule, in accordance with Standard Protocol Items: Recommendations for Interventional Trials (SPIRIT) guidelines, is outlined in table 1.

**Table 1 T1:** Proposed data collection schedule according to SPIRIT guidelines

	Pre-trial		Trial period			
	Week 0		Week 1	Weeks 2–5	Week 6	3 Months
	Eligibility, informed consent	Baseline questionnaire, random allocation	Intervention onboarding	Intervention period	Follow-up 1	Follow-up 2
**Pre-enrolment**						
Screening						
Inclusion/exclusion criteria	X					
WhipPredict	X					
K6 (Kessler Psychological Distress Scale)	X				X	X
Participant information and informed consent	X					
**Baseline assessment and randomisation**						
Baseline questionnaire		X				
Randomisation		X				
Interventions/comparator						
Intervention onboarding			X			
Welcome message			X			
Phone call (RISE only)			X			
Onboarding messages			X			
Wearable device delivery and set-up check (RISE only)			X			
SMS interventions						
RISE intervention						
Tailored daily messages				X		
My Whiplash Navigator access				X		
Weekly check-in and diary entry				X		
Optional psychologist session				X		
Optional physiotherapist session				X		
Wearable use				X		
Optional continuation SMS				X		
Active control				X		
General health messages				X		
My Whiplash Navigator access				X		
**Assessments**						
Expectancy and acceptability						
Credibility/Expectancy Questionnaire		X				
Acceptability (Technology Acceptance Questionnaire and purpose-built items)		X			X	X
Session Rating Scale (RISE only)				X		
Blinding assessment (perceived group allocation)					X	
Pain and disability						
Pain tolerability and comfort		X			X	X
Pain intensity (Brief Pain Inventory)		X			X	X
Neck Disability Index (NDI)		X			X	X
Psychological						
DASS-21		X			X	X
Post-Traumatic Stress Disorder single items*		X			X	X
Primary care PTSD screen		X			X	X
PCL-5 (only if PTSD screening is positive)		X			X	X
Quality of life and well-being						
EQ-5D-5L		X			X	X
Global Impression of Change					X	X
Cost-related						
Health service and medication use		X			X	X
Compensation claim and lawyer involvement		X			X	X
Work/income status		X			X	X

* These items guide the tailoring of the messages.

DASS-21, 21-item Depression Anxiety and Stress Scale; EQ-5D, EuroQol-5 Dimension (health-related quality of life); GIC, Global Impression of Change; PCL-5, PTSD Checklist for DSM-5 ; PTSD, Post-Traumatic Stress Disorder; RISE, recovery, information, support and empowerment; SMS, short message service; SPIRIT, Standard Protocol Items: Recommendations for Interventional Trials.

